## Abstract

**Background:**

Siblings of individuals with first episode psychosis are natural partners to promote service users’ recovery and are themselves vulnerable to mental ill health due to the negative impact of psychosis within the family. This study aims to develop and undertake a preliminary evaluation of the efficacy of an online multi-component psychoeducational intervention for siblings of individuals with first episode psychosis. The impetus for the intervention arose from siblings' expressed needs for peer support and information on psychosis, coping and management strategies for common symptoms and ways to promote recovery.

**Methods/Design:**

The project design draws on the Medical Research Council framework for the design and evaluation of complex interventions. Mixed methods comprising collection of qualitative focus group data, systematic review and expert advisory group consultation are used to develop the theoretical basis for and design of the intervention. This protocol focuses on the modelling and piloting phase which uses a randomised controlled trial with factorial design to test the efficacy of the intervention. Outcome data on participants’ mental wellbeing, knowledge, perceived self-efficacy and experiences of caregiving will be assessed at baseline, at end of the intervention (10 weeks later) and at 10 week follow-up. In addition, a post-intervention semi-structured interview with 20% of the participants will explore their experiences and acceptability of the intervention.

**Discussion:**

This multi-component online psychoeducational intervention aims to enhance siblings' knowledge about psychosis and their coping capacity, thus potentially improving their own mental wellbeing and promoting their contribution to service users’ recovery. The factorial design randomised controlled trial with a supplementary process evaluation using semi-structured interviews and usage-monitoring will collect preliminary evidence of efficacy, feasibility and acceptability, as well as feedback about the barriers and strategies to using such an innovative resource. The RCT will provide data for estimating the likely effect size of the intervention on outcomes for siblings and inform the development of a definitive future trial.

**Trial registration:**

Trial registration:
ISRCTN01416694

## Background

Over 80% of the general population in the U.K. has at least one sibling, and the sibling relationship often outlives any other kind of relationship, including marriages and parenthood [1]. Siblings share *‘a common social, cultural and genetic heritage that often reaches into old age’*[2]. As such, the sibling relationship can be particularly influenced or influential when one sibling develops a severe mental illness. It has been argued that the quality of the sibling relationship, especially during adolescence and early adulthood, is a predictive factor in the siblings’ future involvement in caring for their brother or sister with severe mental illness [3], as well as being associated with a higher quality of life [4] and a more promising recovery trajectory [5,6] in individuals with a diagnosis of psychosis. However, despite the significance of the sibling relationship and policy guidelines advocating a family inclusive approach across mental health services, especially Early Intervention in Psychosis Services (EIPS) [7], front-line service provision falls short in this respect. There remains a paucity of research into effective interventions for siblings of individuals with first episode psychosis (FEP) [8-10].

Psychoeducation, information-giving on the condition and its management [7,11], is among the most effective of the evidence-based psychological interventions that has long been implemented as both an individual and a group approach to service users of severe mental illness and their family members or carers (see [11] for an updated Cochrane Review). It is frequently hypothesised that the effectiveness of psychoeducation can be explained by its impact on knowledge, on stress appraisal and on coping, and subsequently perceived subjective burden and self-efficacy (for example: [12,13]); so building upon the theory of stress and coping first coined by Lazarus in the 1960s [14]. Meanwhile, a recent qualitative research study of FEP siblings’ needs and experiences [9,15] highlighted siblings’ needs for robust, dynamic and accessible psychoeducational information on psychosis, coupled with peer support, practical coping and management strategies for common psychotic signs and symptoms, adjustment to loss and changes, and ways to promote recovery in their ill brother or sister. Most siblings reported experiencing a range of emotions, for example: worry, guilt, loneliness and stigma, that affect their own wellbeing, whilst some also reported developing resilience within themselves and their families [6,9].

Traditional and conventional psychoeducation delivery through face-to-face sessions with mental health professionals or accessed through statutory mental health services has failed to reach siblings successfully hitherto [9,15,16]. A high proportion of siblings of individuals diagnosed with FEP are in full-time education or are of working age and many have busy lives. Thus any service development targeting siblings demands flexible, dynamic and innovative measures using modern information and communication technologies [17]. There is a handful of research studies showing promising benefits for multi-component online psychoeducational interventions, covering a range of long-term and severe diseases including dementia, diabetes, and cancer. Multi-component interventions for these conditions commonly include: information sharing, networked peer support, electronic resources and facilitated discussion forums [18]; but much less work has been done in the field of severe mental illness [19,20]. To date, there are only three known exploratory controlled trials evaluating online psychoeducational interventions with service users with psychosis and their family carers in the U.S.A. [19,21,22] and with service users with bipolar disorder in Australia [23]. In the UK, a few online blogs and information-giving websites have been established by leading charities over the last few years (for example: http://www.sibs.org.uk[24] and http://www.rethink.org/siblings[25]). However, there is no known evaluative study of any such intervention for people with severe mental illness and their families, let alone siblings.

### Justification and rationale of the current project

The need for a robust, flexible and effective psychoeducational intervention that also provides an element of peer support for siblings especially when they are in their late teenage and early adulthood is clear [9,16]. There have been a number of successful and effective online psychoeducational interventions for service users and their family members across a wide range of long-term severe illness, but such interventions are under-developed in the mental health field. A few charities in the U.K., Australia, Canada and the U.S.A., prompted by siblings’ own initiatives and demands, have been running information-giving and network support web-sites for siblings over the last few years. However, there are no known evaluations of the impact of these initiatives. In a time of evolving technological advances and ever-increasing emphasis on cost-effective and evidence-based interventions promoting self-management, development of an online psychoeducational intervention incorporating various components and resources indicated for this population together with a rigorous evaluation, is timely.

### Aims of the project

This paper describes the rationale and protocol for a factorial designed randomised controlled trial targeting siblings of young people diagnosed with FEP who are receiving support from local EIPS. The aims of the overall “E Sibling Project” are to:

I. Develop a multi-component resource combining health information and peer support enlisting research evidence and siblings’ views.

II. Optimise the IT and e-learning technologies in the design and delivery of the intervention.

III. Undertake a preliminary evaluation of the efficacy of the intervention.

The trial has the following objectives:

IV. To optimise the intervention

V. To determine trial parameters

VI. To provide preliminary evidence of the efficacy of the intervention in terms of impact on siblings’ mental wellbeing; knowledge; perceived self-efficacy in coping and experiences in caregiving.

VII. To optimise the design of a future full scale trial

## Methods

The design of this study draws upon the UK Medical Research Council’s complex interventions framework [26] to address the key elements of the development and evaluation of an online multi-component psychoeducational intervention for siblings of individuals diagnosed with FEP. The intervention is “complex” according to the MRC definition [26] because it comprises a number of and interactions between components within the intervention, that subsequently impact on a number of variable outcomes. The components are: psychoeducation and peer support, each of which is a complex intervention in its own right, and each may work independently as well as inter-dependently in exerting their effects. The potential outcomes include: siblings’ mental wellbeing, knowledge, self-efficacy and coping. Another issue for consideration in complex interventions is the number and difficulty of performing behaviours required by those delivering and/or receiving the intervention, such as those involved in this intervention by the sibling-participants. These complexities demand a factorial designed RCT in which not only primary outcomes and multiple secondary outcomes are investigated, but also the process evaluation measures to understand participants’ experiences and actual usage of the intervention. The project comprises a number of phases using mixed research methods, as outlined in Figure 1. The study was reviewed and approved by UK NHS Research Ethics Committee process (REC approval reference number: 12/LO/1537).

**Figure 1 F1:**
[figure not shown]
Design of the study using MRC complex intervention framework, inclusive of time schedule for various phases.

The RCT comprises an exploratory trial, to complete the modelling and piloting phase of the MRC 4-phased framework [26]. The RCT employs a 2 by 2 factorial design, as illustrated by Figure 2. The factorial design gives the RCT 4 arms: 3 treatment conditions (covering: psychoeducation alone; peer support alone; and combined psychoeducation and peer support) and a control condition. This design is chosen to fit with the two active components in the intervention, i.e. psychoeducation and peer support. Considering that these two ingredients may work independently as well as inter-dependently, the three treatment arms allow an investigation not only to determine the effectiveness of the combined psychoeducation and peer-support treatment condition, but also of how each ingredient impacts independently on particular participants’ outcomes, minimising any contamination [26,27]. Hence, the factorial design RCT will aid our theoretical understanding of the intervention, how it works, how its ingredients interact with each other and ultimately how it supports changes in the targeted outcomes. Furthermore, the results using the factorial design will inform the optimal intervention to be used in the full scale trial.

**Figure 2 F2:**
[figure not shown]
Progression of participants through the phases of the trial.

### Design

#### Randomisation, treatment allocation and blinding

This is a factorial design RCT in which participants are randomised and allocated to 4 conditions: 3 treatment conditions in addition to treatment as usual (control). The three treatment arms will allocate participants into either: psychoeducation alone; peer support alone; or combined psychoeducation and peer support. Screening for eligible participants against inclusion and exclusion criteria is conducted online through screening questionnaires. All eligible participants will then be allocated to one of the three treatment or the control condition. Randomisation is done using computer-generated permuted blocks and is carried out by an independent Clinical Trial Unit (CTU) to ensure blindness. Eligible participants will receive a computer-generated account with username and a unique password as well as the treatment group they have been allocated to.

### Participants

#### Recruitment & Informed consent

Advertisement and recruitment will be conducted through a website developed and dedicated to delivery of the online information and peer support intervention produced by King’s College London; Early Intervention in Psychosis Services (EIPS); local carers groups and networks; and the Mental Health Research Networks (MHRN) across South-East England, including London. Care co-ordinators and clinicians working in EIPS in five NHS Trusts across South-East England will be given information about the trial in a series of presentation by the trial team. Clinicians will help identify potentially suitable participants from their case load of service users to the trial co-ordinator, with the service users’ and/or potential participants’ consent. The trial co-ordinator will make contact and provide further information about the trial to all potential participants. Individual consent from the participants will be sought following comprehensive information-giving and a consideration period of at least 3 days. Presentations will also be made at (family) carers and siblings events hosted by Rethink Mental Illness and other carers-related organisations/ networks over the period. Interested siblings may refer themselves directly to the research team to join the trial after the same information-giving, consideration and screening process.

Each of the five NHS Trusts covers a population of about one million and each has an EIPS caseload ranging from 400 to 600 service users at any one time. EIPS are dedicated mental health services for people aged between 16 to 35 who are affected by a first-episode psychosis [7]. The provision of service by EIPS usually starts from immediately following the onset of first episode psychosis, a critical period in determining long-time trajectory in recovery [5,7], and the treatment period is usually about three years. Following that, EIPS usually transfer the care of service users back to their GPs or to secondary mental health services for long-term support, e.g. community mental health teams. The time required to recruit 144 participants is estimated as 20 weeks. Contingency plans to address any short-fall in the recruitment include recruitment of additional participants to compensate for anticipated 20% attrition, extra time for recruitment and extension of the recruitment area to additional NHS Trusts within the geographical regions.

#### Inclusion criteria

This trial targets siblings of individuals diagnosed with FEP directly. Hence, 144 siblings will be recruited who fulfill the following inclusion criteria:

&z.squf; aged 16 or above;

&z.squf; has a brother or sister receiving service from a local EIPS at the time of joining the trial;

&z.squf; is based within the Greater London or Berkshire area themselves;

&z.squf; has had contact at least weekly with their ill brother or sister on average over the previous 3 months.

&z.squf; can read and understand English language in usual online communications.

&z.squf; has daily access to internet use.

#### Exclusion criteria

Regrettably, we cannot accept siblings with the following criteria into the trial:

&z.squf; individuals unable to give informed consent;

&z.squf; those affected by a mental illness themselves that requires treatment and care from a secondary/ specialist mental health services (e.g. seeing a psychiatrist at out-patient clinic regularly; under the care of a community mental health team; has a care co-ordinator).

Since the age limit for sibling-participants is aged 16 or above, all participants will be able to consider their own rights and interests and give informed consent without parental guidance or assent. The peak age of first psychotic onset is estimated as late teenage and early adulthood, around 22 years of age in the UK [7]; it is estimated that majority of the siblings for people with FEP who have had direct experience of supporting their brother/sister will have an age range of teenage to young adulthood.

Considering the intervention is an online resource with a mixture of textual, audio and visual information and the trial is a feasibility pilot, the participants are required to have a basic level of ICT and English which are required to make use of the intervention. Nonetheless, IT and technological support will be available through emails and phone-contacts between the participants and an IT support service located in parallel to the research team.

#### Sample size

The exploratory trial is a feasibility pilot study to establish a preliminary estimate of the efficacy of an innovative intervention. The trial is not designed for hypothesis testing [24,25]. The pragmatic sample size of 120 participants for the trial was selected with reference to the general rule of thumb recommended by Lancaster et al. [27], taking account of the factorial design of this exploratory trial and the primary and secondary outcome measures to be investigated. A sample of 30 per arm is considered sufficient to obtain estimates of the values of outcomes for each arm and thus an estimate of the effect size which would then be used to inform the design of a definitive trial. To ensure the rule of thumb minimum sample of 30 will be retained in each arm, additional participants (i.e. N=144, n=36 in each arm) will be recruited to allow for an estimated attrition rate of up to 20%.

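### Recruiting 36 per arm leaves 28.8 per arm, not the stated minimum of 30, at the 20% attrition the plan allows for (minor; one sentence to correct)

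*Protocol article*

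**What the plan says.** The Sample size section of the protocol article starts from "The pragmatic sample size of 120 participants for the trial", which is 30 in each of four arms, chosen by a rule of thumb. It then gives the aim of the inflation, "To ensure the rule of thumb minimum sample of 30 will be retained in each arm", and the means: "additional participants (i.e. N=144, n=36 in each arm) will be recruited to allow for an estimated attrition rate of up to 20" per cent.

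The figure of 144 returns in the Inclusion criteria section ("Hence, 144 siblings will be recruited who fulfill the following inclusion criteria") and in Recruitment & Informed consent, where the time to recruit that number is put at 20 weeks. The latter section then lists contingencies for a recruitment shortfall: "recruitment of additional participants to compensate for anticipated 20% attrition", more recruitment time, and extension to further NHS Trusts. No section gives a recruitment figure above 144.

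**The concern.** The plan makes one checkable statement about its size: at least 30 per arm remain if attrition is no worse than 20%. Attrition is a loss from those recruited, so the number to recruit is the target divided by the fraction retained. The stated 36 is the target plus 20% of the target, a smaller number that cannot meet the floor at the stated loss.

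Two things are at stake. First, the size has no power calculation behind it, so the retained 30 per arm is its whole stated justification. Second, the Quantitative data section says the trial will supply data for the sample size of a definitive trial. If the same way of inflating for dropout were carried into that trial, it too would recruit too few.

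**Working it through.** **Inputs, all from the protocol article**

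- Minimum to be retained per arm: 30 (Sample size)
- Total before the attrition allowance: 120 (Sample size)
- Planned recruitment: 36 per arm, 144 in total (Sample size; 144 repeated in Inclusion criteria)
- Attrition d: up to 20% (Sample size); 20% also in Recruitment & Informed consent
- Arms: four ("The factorial design gives the RCT 4 arms", Methods), of equal size as the 36 per arm implies

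**1. Reproducing the plan's figure**

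n × (1 + d):

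- per arm: 30 × 1.20 = 36
- total: 120 × 1.20 = 144

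Both stated numbers are matched exactly, so this is very probably how they arose.

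**2. What those numbers retain**

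n × (1 − d):

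- per arm: 36 × 0.80 = 28.8, against 30 (short by 1.2)
- total: 144 × 0.80 = 115.2, against 120 (short by 4.8)

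**3. Attrition that 36 per arm can absorb**

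1 − 30/36 = 6/36 = 16.7%

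**4. Size needed for 30 retained at 20%**

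n / (1 − d):

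- per arm: 30 / 0.80 = 37.5, rounded up to 38; four arms give 152
- total inflated without whole equal arms: 120 / 0.80 = 150
- check: 37 × 0.80 = 29.6 (still below 30); 38 × 0.80 = 30.4

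**5. Effect on precision**

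The width of a confidence interval varies as 1/√n: √(30 / 28.8) = 1.02, about 2% wider.

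**6. Whether 38 per arm would guarantee the floor**

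Here an assumption is added: participants drop out independently, each with probability exactly 20%. The number retained in an arm is then binomial.

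| Recruited per arm | Expected retained | P(one arm keeps ≥ 30) | P(all four arms keep ≥ 30) |
|---|---|---|---|
| 36 | 28.8 | 0.40 | 0.026 |
| 38 | 30.4 | 0.66 | 0.18 |

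The last column is the fourth power of the unrounded single-arm probability. Neither size ensures the floor; 38 meets it on average only.

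**The case against.** The strongest reply is that this hardly matters. The article calls the size pragmatic, takes it from a rule of thumb, and says that the trial is not designed for hypothesis testing. No significance level, power or detectable effect depends on 30 per arm, and intervals 2% wider do not change what a pilot can estimate. This stands, and it sets the severity. It does not make the sentence true.

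A second reply is that 20% is worded as a ceiling in the Sample size section, so actual loss may be lower. At 15%, under the same independence assumption, one arm of 36 keeps at least 30 with probability 0.71. That is fair, but an allowance of up to 20% includes 20%, and Recruitment & Informed consent describes 20% as anticipated.

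Three stronger readings are tempting and are not supported:

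- **That the 0.026 in the table measures the error.** Most of it comes from a stricter test, in which all four arms must clear 30 under random dropout at exactly 20%. The corrected 38 per arm reaches only 0.18 on that test. The error itself is 28.8 against 30.
- **That the recruitment contingency counts the same 20% twice and so protects nothing.** It may restate the allowance inside the 144, or it may mean recruiting beyond 144; the text does not settle which. It gives no number, so it does not repair the calculation, but it cannot be called empty either.
- **That the trial is underpowered or its validity is threatened.** There is no power claim for the shortfall to undermine.

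**Conclusion.** The point holds as an arithmetic error in a stated property of the design. At the plan's own 20% attrition, 36 per arm leaves 28.8 per arm and 115.2 in total, below the 30 and 120 that the Sample size section sets out to secure. The floor holds only up to 16.7% attrition.

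This conclusion needs nothing beyond the document's figures, equal arms, and the ordinary meaning of attrition as a share of those recruited. Only the probabilities in step 6 rest on more, namely independent dropout at a fixed 20%. They serve to show that the word ensure is too strong for 36 and for 38 alike.

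Severity is minor. It is a false statement to correct, not a reason to change the design.

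**What to change.** **Preferred: keep N=144 and reword one sentence in Sample size.** Either of these is accurate:

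- 36 per arm retains 30 if attrition does not exceed 16.7%; or
- at 20% attrition, about 29 per arm (115 in total) are expected to remain.

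This costs no participants.

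**Alternative: keep the floor of 30 at 20% attrition.** Recruit 38 per arm, 152 in total, and change 144 wherever it appears. This costs 152 − 144 = 8 participants. At the planned pace of 144 in 20 weeks (7.2 a week) that is 8 / 7.2 = 1.1 weeks more. The wording should then say that 30 per arm are expected to be retained, since 38 does not guarantee it.

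**In either case, reconcile Recruitment & Informed consent with Sample size.** State whether the extra recruitment for 20% attrition is the allowance already inside 144 or goes beyond it, and give the upper number if it goes beyond. The contingency should not simply be deleted, because it may be real over-recruitment that would help to meet the floor.

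When the definitive trial is sized, inflate for dropout by dividing by the expected fraction retained.
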